### Data management and statistical analysis plan

Data recorded in printed forms are kept in locked cabinets. Information is entered on Microsoft Excel spreadsheets by one person and reviewed by another. Numeric continuous variables, including blood pressure in the primary outcome measures, will be described as mean ± standard deviation or as median (interquartile range). Comparison between groups will be performed using Student’s *t* test or the Mann–Whitney U test, depending on variable distribution. As a superiority trial, differences in autonomic cardiovascular control and metaboreflex between groups will be tested with two-sided repeated-measures ANOVA. Results will be analyzed as per intention-to-treat. Participants who drop out and do not complete outcome assessment will be compared with those who completed the protocol but their data will be excluded from analysis. Statistical significance will be considered for *P* < 0.05. All analyses will be performed using PASW Statistics 18® (International Business Machines Corp., New York, NY).

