### Study outcomes

The co-primary outcomes measures are changes from baseline to end of study in mean 24 h systolic and diastolic blood pressure, as evaluated by ambulatory blood pressure monitoring.

Secondary outcome measures are changes from baseline to end of study in mean daytime systolic and diastolic blood pressure; changes from baseline to end of study in mean nighttime systolic and diastolic blood pressure; heart rate variability; systolic blood pressure variability; aerobic capacity; inspiratory metaboreflex; and autonomic control.

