### Sample size calculation

Sample size was estimated based on a small randomized clinical trial on the effect of inspiratory muscle training on blood pressure of hypertensive subjects in Brazil [13]. That study found an 8 mmHg difference in systolic blood pressure between the active treatment and the control group (standard deviation, 10 mmHg). To detect this difference with power of 80 %, and assuming an alpha error of 5 %, the study should include 26 participants per group. We opted for a 20 % inflation of this number to account for loss of follow-up and consent withdrawal – therefore, a total of 60 participants will be included and assigned to either intervention or sham treatment.

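### The co-primary blood pressure comparison does not adjust for baseline 24 h pressure; adding baseline as a covariate is a free gain in precision

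*Protocol article*

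**What the plan says.** Under *Study outcomes*, the protocol article states: "The co-primary outcomes measures are changes from baseline to end of study in mean 24 h systolic and diastolic blood pressure". Both are measured by ambulatory monitoring, so a baseline 24 h value is needed from every participant who contributes to the primary analysis.

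Under *Data management and statistical analysis plan*, the article names the primary blood pressure measures among the continuous variables. It then says "Comparison between groups will be performed using" a Student t or a Mann–Whitney test, chosen by distribution. The only other model is kept for different outcomes: "differences in autonomic cardiovascular control and metaboreflex between groups will be tested with two-sided repeated-measures ANOVA". No baseline covariate is given for blood pressure.

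Under *Sample size calculation*, the planning values come from one small earlier trial: "That study found an 8 mmHg difference in systolic blood pressure between the active treatment and the control group" ("standard deviation, 10 mmHg"). With 80% power and 5% alpha, these give 26 per group. The article does not say whether the SD belongs to the change or to a single 24 h mean.

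**The concern.** Baseline 24 h pressure is likely to predict both the week-8 value and the change. A change score removes baseline with a coefficient fixed at 1. The best linear coefficient is the regression slope of week 8 on baseline, which is usually below 1. Where the slope is below 1, the change score over-corrects: the arm that happens to start higher tends to show the larger fall through regression to the mean. In a trial of 52 to 60 people, that noise enters the treatment estimate and widens its interval.

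The trial already collects the covariate that would remove this noise. The article states the method, so this is a choice that can be improved and not a detail left to a document not shown.

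**Working it through.** **Inputs.** From *Sample size calculation*: difference 8 mmHg, SD 10 mmHg, power 80%, alpha 5%, 26 per group. Assumed, because the document does not give them: the correlation r between baseline and week-8 24 h systolic pressure, equal SDs at the two visits, and what the SD of 10 refers to.

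**Step 1: reproduce the plan's figure.** A two-sided two-sample t test with d = 8/10 = 0.8 (noncentral t) needs n = 25.52, so 26 per group. This matches the article and fits an unadjusted analysis. Power at 26 is 80.7%.

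**Step 2: variance ratio.** Let s be the common SD.

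- Change score: variance 2(1 − r)s².
- ANCOVA residual: variance (1 − r²)s².
- Ratio, ANCOVA to change score: (1 + r)/2.

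With unequal SDs, let k = SD(week 8)/SD(baseline). In units of the baseline variance, the change score has variance 1 + k² − 2rk and ANCOVA has k²(1 − r²). The difference is (1 − rk)², so the gain disappears when rk = 1.

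**Step 3: power if 10 mmHg is the SD of change.** The ANCOVA SD is 10 × √((1 + r)/2), the noncentrality is (8/SD) × √(26/2), and there are 49 degrees of freedom (one fewer than the t test).

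| r | Variance ratio | ANCOVA SD | Power at 26 per group | n per group for 80% |
|---|---|---|---|---|
| unadjusted | 1 | 10.00 | 80.7% | 26 |
| 0.5 | 0.75 | 8.66 | 90.4% | 20 |
| 0.7 | 0.85 | 9.22 | 86.6% | 22 |
| 0.8 | 0.90 | 9.49 | 84.6% | 24 |
| 0.9 | 0.95 | 9.75 | 82.7% | 25 |

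Simulation (4000 runs each, 26 per group) agrees: power goes from 81.7% to 89.9% at r = 0.5 and from 80.2% to 85.5% at r = 0.7. The simulated variance ratios were 0.78 and 0.89. They lie a little above the formula because the slope is estimated, which adds a factor of about 1 + 1/(2 × 26 − 4) = 1.02, and because of simulation error.

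**Step 4: power if 10 mmHg is the SD of a single 24 h mean.** The change SD is 10√(2(1 − r)) and the ANCOVA SD is 10√(1 − r²).

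| r | Change SD | ANCOVA SD | Power, change score | Power, ANCOVA |
|---|---|---|---|---|
| 0.3 | 11.83 | 9.54 | 66.7% | 84.2% |
| 0.5 | 10.00 | 8.66 | 80.7% | 90.4% |
| 0.7 | 7.75 | 7.14 | 95.5% | 97.7% |

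**Step 5: the same loss seen as imbalance.** With equal SDs, a baseline difference D between arms shifts the change-score estimate by (1 − r)D in size. Taking s = 10, one standard error of D is 10 × √(2/26) = 2.8 mmHg. The shift is then about 1.4 mmHg at r = 0.5 and 0.8 mmHg at r = 0.7, against a target of 8 mmHg. If 10 is the SD of change, s at r = 0.7 is 10/√0.6 = 12.9, and the shift is about 1.1 mmHg.

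All power figures are for the t test. None applies to the Mann–Whitney option.

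**The case against.** The strongest reply is that nothing here is wrong. The unadjusted test is unbiased over randomization, holds its type I error, and matches the method behind the 26 per group. Chance imbalance averages to zero, and the unadjusted interval already allows for it. All of that stands.

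The size of the gain is also open to challenge. The ratio (1 + r)/2 needs equal SDs. With r = 0.8 and k = 1.25, the change variance is 1 + 1.5625 − 2 = 0.5625 and the ANCOVA variance is 1.5625 × 0.36 = 0.5625, so there is no gain. Equal SDs are not assured here: *Eligibility criteria* sets both a lower pressure threshold and an upper office limit, which may narrow the baseline spread. How far this carries over to 24 h values is unknown. At r = 0.9 the gain is about 2 power points. These limits stand too, and they are why the result is shown as a range.

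Three stronger readings are tempting but unsupported:

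- **That the analysis ignores baseline.** It does not, because *Study outcomes* defines a change score.
- **That ANCOVA is more efficient for every correlation below 1.** That holds only with equal SDs.
- **That this choice leaves the trial underpowered.** At 26 per group the stated power reproduces, and at the 30 per group enrolled it is 86.1% unadjusted. If 20% of 60 are lost, 24 per group remain, and unadjusted power is 77.4% (with 10 as the SD of change). That shortfall comes from the allowance for losses, which is a separate matter.

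One could also say that covariates belong in a fuller plan. This is weak, because the article itself names the test.

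**Conclusion.** The point holds as an improvement in efficiency and does not correct an error. The article fixes an unadjusted comparison of change for both co-primary outcomes, although the baseline value is in hand. Under equal SDs, and with 10 mmHg as the SD of change, ANCOVA removes 5% to 25% of the variance over r = 0.9 down to 0.5. That is worth about 2 to 10 power points at 26 per group. On the other reading of the SD, the gain runs from about 17 points at r = 0.3 to about 2 at r = 0.7.

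Wider interval and sensitivity to chance imbalance are one effect and should not be counted twice. The reading of the text is firm. The size of the gain is uncertain, because r, the SD ratio and the meaning of the SD are all missing from the document. The calculations use the systolic planning values; the article gives none for diastolic pressure. A reader should not conclude that the planned test is invalid or its result biased.

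**What to change.** Prespecify as the primary analysis, separately for 24 h systolic and 24 h diastolic pressure, a linear model of the week-8 value (or the change, which gives the same treatment effect) on arm and the baseline 24 h value of the same pressure. Report the adjusted mean difference with its 95% CI. Keep the unadjusted comparison as a sensitivity analysis.

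The change is to wording only. It costs one degree of freedom and no extra data, and a linear model of this kind is standard in the named software. It should be recorded before assignments are released. *Randomization, allocation, blinding, and confidentiality* places that release after data collection is complete, and *Trial status* reports that enrolment was still open at publication. It is a free improvement.

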### Randomization, allocation, blinding, and confidentiality

A randomization sequence has been generated using Randomization.org in blocks of four to either group 1 – inspiratory muscle training with 40 % of maximal inspiratory pressure – or group 2 – sham inspiratory muscle training. An independent person not involved in this study possesses the computer-generated randomization sequence. A research assistant not involved in participant assessment obtains the code and sets the load in each device, according to randomization. A black tape hides the loading spring from the participant and from the investigators assessing outcomes.

There are no foreseen circumstances when un-blinding is permissible. When data collection is completed, the person responsible for the randomization list will provide assignment information to the investigators. Patient’s forms and other data sources are kept in a locked cabinet. Data are anonymized when entered into the database to protect confidentiality. Only investigators formally associated with the project will have access to the final study database.

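### The test and summary for the co-primary 24 h blood pressures depend on the data's distribution, so the primary effect measure is not fixed and may differ between systolic and diastolic pressure

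*Protocol article*

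**What the plan says.** All references are to the protocol article.

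- **Study outcomes:** "The co-primary outcomes measures are changes from baseline to end of study in mean 24 h systolic and diastolic blood pressure", measured by ambulatory monitoring.
- **Data management and statistical analysis plan, summary:** numeric continuous variables, "including blood pressure in the primary outcome measures, will be described as mean ± standard deviation or as median (interquartile range").
- **Same section, test:** the between-group comparison uses "Student’s *t* test or the Mann–Whitney U test, depending on variable distribution".
- **Same section, other outcomes:** "differences in autonomic cardiovascular control and metaboreflex between groups will be tested with two-sided repeated-measures ANOVA". This sentence does not extend to the blood pressure outcomes, so the t or Mann–Whitney sentence is the only one that governs the primary comparison.
- **Sample size calculation:** "That study found an 8 mmHg difference in systolic blood pressure between the active treatment and the control group" ("standard deviation, 10 mmHg"), 80% power, 5% alpha, 26 per group.

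**The concern.** This is a stated rule, not an omission. The distribution of the data picks both the test and the summary for the primary outcomes, and the two options do not answer the same question. The t test concerns a difference in means in mmHg. Mann–Whitney concerns whether values in one arm tend to exceed those in the other, and a median with interquartile range supplies no mean difference.

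Three things follow.

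- The primary effect measure is unknown until the data are seen.
- Nothing requires the same choice for systolic and diastolic pressure, so the co-primary results could sit on different scales.
- If ranks are chosen, the primary result no longer directly estimates the quantity behind the sample size.

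**Working it through.** **1. Which analysis the sample size assumes.** Inputs from Sample size calculation: difference 8 mmHg, SD 10 mmHg, power 80%, alpha 5%. The section does not state sidedness.

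- Normal approximation, two-sided: n = 2 × (1.96 + 0.84)² × 10² / 8² = 24.5, so 25 per group.
- Noncentral t, two-sided, standardised difference 8/10 = 0.8: n = 25.52, so 26 per group. This is the protocol's figure.
- One-sided, normal approximation: 20 per group, which does not match.

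The stated 26 is therefore what a two-sided t test on a difference in means requires. With 26 per group its power is 80.7%.

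**2. How the selection rule behaves.** The article names no criterion, so the following are assumptions: 26 per arm; Mann–Whitney replaces the t test if Shapiro-Wilk gives P < 0.05 in either arm; changes are normal, t-distributed on 5 df, or lognormal with sigma 0.5; the true difference is 0 or 0.8 SD. Each setting had 6,000 to 8,000 simulated trials. Figures are for one outcome unless stated.

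| | Normal | t on 5 df | Lognormal |
|---|---|---|---|
| Switch to Mann–Whitney fires | about 10% | about 40% | 87–89% |
| The two tests disagree on significance, planned effect | about 5% | about 9% | 11–12% |
| Switch fires **and** changes significance, planned effect | about 0.7% | about 6% | about 11% |
| Power, t test fixed in advance | about 81% | about 81% | about 81% |
| Power, rule as written | 80–81% | about 86% | 91–92% |

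- The 10% switch rate with normal data is what two independent 5% checks give: 1 − 0.95² = 9.75%. A single check on pooled residuals would give about 5%.
- The second row counts every disagreement, including trials in which no switch occurs. The third row measures the effect of the rule itself.
- Type I error of the rule, applied as written, lay between 4.6% and 5.7% across all runs and distributions.

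**3. Different tests for the two outcomes.** With an assumed systolic–diastolic correlation of 0.5 to 0.8, the two co-primary outcomes received different tests in about 16–18% of trials when both were normal, and in about 18–20% when both were skewed.

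**The case against.** The strongest reply is that the rule does little statistical damage and can help. Much of that stands.

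- **Error rate.** A reader might infer that choosing the test from the data inflates type I error. Applied as written, the rule does not do so materially. Inflation would need the test to be picked by its P value, and the plan says the choice depends on distribution.
- **Benefit of switching.** A reader might call the switch useless. It is not: with heavy tails or skew it raises power from about 81% to 86–92%. That gain belongs to a different hypothesis, however, and the fixed t test keeps about 80% power in every setting examined.
- **Wording of the outcome.** A reader might say that Study outcomes defines a group mean change as primary. There, the 24 h mean is each participant's own average over the recording. The group mean difference is implied by the sample size, not defined word for word.
- **Unblinding.** After data collection, the holder of the list "will provide assignment information to the investigators". A reader might infer that the test will be chosen with allocation known. The article does not say when distributions are examined, so this cannot be asserted as a defect.
- **An unseen analysis plan.** The normality criterion may well be set out elsewhere, and its absence here is no finding. A criterion would not cure the problem, because the stated rule would still let the data choose the effect measure.
- **Reporting.** Using Mann–Whitney does not forbid also giving a mean difference in mmHg. True, but the rank test would then not be a test of that difference.

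**Conclusion.** The point holds in a limited form. The article does not fix one test and one summary for the co-primary outcomes, so the effect measure is open, the two outcomes may be reported on different scales, and a rank-based result would not directly estimate the mean difference that the trial is sized to detect. The practical effect on significance is small if changes are roughly normal (about 0.7% of trials) and larger if they are not (about 6% for t on 5 df, 11% for lognormal skew). These percentages rest on the assumed per-arm Shapiro-Wilk trigger and the assumed shapes; the article gives no figure on the shape of the changes. Type I error stays near 5%, and 26 per group remains correct for the mean-based test. The change is worth making for clarity of the primary result, but the trial's validity does not hang on it.

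**What to change.** For both co-primary outcomes, delete the clause that makes the test depend on distribution, and remove the mean-or-median option for them. Prespecify one analysis for both: the between-group difference in mean change in mmHg with a 95% CI, from a linear model adjusted for the baseline 24 h value. Keep Mann–Whitney as a supportive sensitivity analysis. The essential step is to fix one mean-based analysis; baseline adjustment is a sensible way to do it with data already collected.

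The cost is about one sentence. No extra participants are needed, and the article's Trial status section says that enrolment is still under way. The downside is some loss of power compared with ranks if changes are markedly heavy-tailed or skewed, although the mean-based test keeps about 80%.

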### Study design

This is a double-blind, parallel-group, sham-controlled randomized clinical trial. Participants are randomly assigned to receive inspiratory muscle training with a load equivalent to 40 % of maximum inspiratory pressure or inspiratory muscle training sham (no load) for 8 weeks. The study flowchart is depicted in Fig. 1. Participants are followed on weekly visits. Study outcomes are assessed at the end of the eighth week. The study timeline is summarized in Additional file 1: Figure S1, where detailed information on methods of assessment and protocols can be found.

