### Studied variables and methods of assessment

Participants are assessed as described in Additional file 1. Briefly, baseline physical activity is quantified using the International Physical Activity Questionnaire long form [20]. Body mass index is calculated as mass (kg) divided by the square of the height (m) and categorized as recommended by the World Health Organization [21]. Ambulatory blood pressure monitoring is performed with Spacelabs 90207 devices (Redmond, WA, USA). The protocol includes blood pressure measurement every 15 min during the daytime (6 a.m. to 10 p.m.) and every 20 min during the nighttime (10 p.m. to 6 a.m.) [22]. Functional capacity is assessed during exercise through O_2_ and CO_2_ expiration fraction in a metabolic system. Maximum oxygen consumption in each breath is recorded in ml/(Kg/min) [23, 24].

Maximum inspiratory and maximum expiratory pressure serve as indicators of inspiratory and expiratory muscle strength, respectively. Maximum inspiratory and maximum expiratory pressure are assessed using a digital pressure manometer (MVD-300, Microhard System, Globalmed, Porto Alegre, Brazil) [25, 26].

Inspiratory muscle endurance is determined using the incremental test proposed by Martyn et al. [27] using the Powerbreathe Plus® system (London, UK). The test is stopped when the subject cannot open the inspiratory valve or desires to stop the test owing to respiratory exhaustion (quantified using the modified Borg scale).

Blood pressure variability, heart rate variability, and the cardiac vagal tone are assessed to evaluate autonomic cardiovascular control. Non-invasive continuous blood pressure curves, heart rate, and electrocardiogram tracing are obtained simultaneously at a frequency of 1000 Hz using a Biopac MP150 (Biopac, California, EUA). Data are registered in a computer with biologic signal conversion capabilities.

The muscle metaboreflex is the adaptive blood flow redistribution from the peripheral circulation into the vascular bed of metabolically active (exercised) muscles [28]. The metaboreflex intensity is inversely related to one’s fitness. Inspiratory muscle metaboreflex is assessed by causing diaphragmatic fatigue and detecting peripheral blood flow reduction [28, 29]. Monitored parameters include: oxygen saturation, carbon dioxide partial expiratory tension, mean arterial pressure, and venous occlusion plethysmography. A detailed protocol can be found in Additional file 1.

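### The repeated-measures ANOVA for the autonomic and metaboreflex outcomes names no tested term; its wording permits a diluted one, and a baseline-adjusted week-8 comparison would be more efficient on either reading

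*Protocol article*

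**What the plan says.** The Protocol article, section Data management and statistical analysis plan, gives two rules for comparing the arms. The general one is "Comparison between groups will be performed using Student’s *t* test or the Mann–Whitney U test, depending on variable distribution". The specific one is "differences in autonomic cardiovascular control and metaboreflex between groups will be tested with two-sided repeated-measures ANOVA". The second rule does not say whether the group term or the group-by-time term carries the test, which time points enter, or how baseline is used.

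On timing, Study design states: "Study outcomes are assessed at the end of the eighth week". Together with the baseline assessment, this suggests two visits per outcome.

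On which outcomes belong to which rule, two sections differ. Study outcomes lists, as separate items, "heart rate variability; systolic blood pressure variability; aerobic capacity; inspiratory metaboreflex; and autonomic control". Studied variables and methods of assessment says: "Blood pressure variability, heart rate variability, and the cardiac vagal tone are assessed to evaluate autonomic cardiovascular control". The first sets the variability measures apart from autonomic control; the second makes them its components.

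**The concern.** A repeated-measures ANOVA with two arms and a time factor yields a group term, a time term and a group-by-time term. A difference between groups, taken literally, is the group term. If baseline is one of the repeated levels, that term compares the arms on the average of baseline and week 8. Randomisation makes the baseline difference zero in expectation, so the average dilutes the treatment effect.

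These outcomes matter to the trial's argument. The study aim names sympathetic modulation and the metaboreflex as the proposed mechanism, and the Discussion counts the metaboreflex evaluation as a strength. A diluted test could lead to a negative mechanistic conclusion when the training does have the effect. If the test for the variability outcomes is not fixed in advance, the choice could also be made after the data are seen.

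**Working it through.** **Inputs from the Protocol article.**
- Planning values for systolic blood pressure: difference 8 mmHg, SD 10 mmHg, so d = 8/10 = 0.8 (Sample size calculation). The article gives no effect size for the autonomic or metaboreflex outcomes, so 0.8 serves only as a scale.
- "To detect this difference with power of 80 %, and assuming an alpha error of 5 %, the study should include 26 participants per group".
- Allocation "in blocks of four to either group 1" or group 2, from which equal arms are inferred.
- One end-of-study assessment at week 8; two-sided test at 5%.

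**Assumed.** The correlation r between a participant's baseline and week-8 values is not given. It is varied from 0 to 0.8. Both visits have SD 1, and each participant has one value per visit.

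**The plan's own figure.** The normal approximation gives 25 per group. The noncentral t gives power 79.1% at 25 and 80.7% at 26. The stated 26 is therefore reproduced for a t test.

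**Three candidate tests**, with the true arm difference 0 at baseline and d at week 8:
1. Group main effect: a t test on each participant's mean of the two visits. Expected difference (0 + d)/2 = 0.40; variance (1 + r)/2; standardised effect 0.40/√((1 + r)/2).
2. Group-by-time: a t test on change. Expected difference d = 0.80; variance 2(1 − r); standardised effect 0.80/√(2(1 − r)).
3. Week-8 value adjusted for baseline (ANCOVA): expected difference 0.80; residual variance 1 − r²; standardised effect 0.80/√(1 − r²). This is approximate, because it ignores the degree of freedom spent on baseline and chance baseline imbalance.

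Power is from the noncentral t with 50 degrees of freedom and noncentrality (standardised effect) × √(26/2). At r = 0.5, for example, the group term has 0.40/√0.75 = 0.462, group-by-time has 0.80/√1 = 0.800, and ANCOVA has 0.80/√0.75 = 0.924.

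| r | Group term | Group-by-time | Baseline-adjusted |
|---|---|---|---|
| 0 | 51.6% | 51.6% | 80.7% |
| 0.3 | 41.9% | 66.7% | 84.3% |
| 0.5 | 37.2% | 80.7% | 90.4% |
| 0.7 | 33.5% | 95.5% | 97.7% |
| 0.8 | 32.0% | 99.4% | 99.7% |

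**Checks.** In 20,000 simulated trials the group-term estimate averaged 0.402 at r = 0.5 and 0.399 at r = 0.7, against a true 0.80, with rejection rates of 37.0% and 33.4%. Group-by-time rejected in 80.5% and 95.4%. On one simulated data set the group-by-time F and the squared change-score t were both 11.888, which confirms that they are the same test.

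**What the table shows.** Halving the estimate does not by itself cost power against group-by-time: the two terms tie at r = 0, and the gap opens as r rises. The variance of the baseline-adjusted contrast relative to the change score is (1 − r²)/(2(1 − r)) = (1 + r)/2, which is 0.5 at r = 0, 0.75 at r = 0.5 and 0.85 at r = 0.7. Baseline adjustment is therefore more efficient throughout the range, though the gain shrinks as r rises.

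**The case against.** The strongest reply is that the article never says the group main effect is the test. Comparing groups by repeated-measures ANOVA is also ordinary shorthand for group-by-time, and the definition of the blood pressure outcomes as changes from baseline fits that reading. This stands. A reader might infer that the plan has chosen a test that halves the effect, but the text does not support that: the halving follows from one permitted reading.

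Second, a journal article may leave the model term to an analysis plan that is not shown. This also stands, and the unnamed term alone would not be a finding. What remains is that the method as stated can be improved on whichever term is meant.

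Third, the repeated factor may be stages within a metaboreflex session, described in Additional file 1 (not shown). The factor of one half could then differ, and if only week-8 stages entered, baseline would not be in the group term at all. This stands as a limit on the figures. For the same reason, a claim that the ANOVA would drop people with one missing stage would be speculative: the visible text describes no stages, and participants who do not complete outcome assessment are already excluded.

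Fourth, a reader might infer that two tests are prescribed for heart rate variability. The specific ANOVA sentence can be taken to override the general rule, and with two visits a t test on change is the same test as group-by-time. What stands is a small ambiguity. The two rules diverge if the general one is applied to week-8 values alone or through the Mann–Whitney test, or if the group term is used.

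Fifth, group-by-time is valid under randomisation. That is true; the case for adjustment is efficiency, not validity.

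**Conclusion.** The point holds in a limited form. The stated ANOVA leaves open a group term that, with one baseline and one week-8 value, estimates exactly half the treatment effect. In the illustration its power is between 32% and 52% over r from 0.8 to 0. If group-by-time is meant, nothing is halved, but power is still below that of a baseline-adjusted comparison: by about 29 percentage points at r = 0 (80.7 − 51.6), 10 at r = 0.5 (90.4 − 80.7) and 2 at r = 0.7 (97.7 − 95.5).

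These sizes rest on a borrowed effect of 0.8 SD, equal variances, 26 analysed per arm and assumed correlations. They illustrate the choice and do not forecast the trial's power for these outcomes. The overlap of rules for the two variability outcomes is real but minor. Only secondary outcomes are concerned; this point does not touch the co-primary 24 h blood pressure analysis.

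**What to change.** For each autonomic and metaboreflex outcome, state one test: the week-8 difference between arms adjusted for the participant's own baseline value, reported with a 95% CI. Use ANCOVA where there is one value per visit. If a session has several stages, use a mixed model of the week-8 values with arm, stage and arm-by-stage, adjusted for the matching baseline value, and name the arm contrast that carries the test. State that heart rate variability and systolic blood pressure variability are analysed by this method only, so that the outcome list and the assessment section lead to the same test.

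The cost is a change of analysis wording. No extra data or participants are needed, and the named software fits these models. The article reports that enrolment was continuing and that assignments are released only after data collection is complete, so the wording can be settled before the investigators learn the allocation.

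### The plan names intention-to-treat but excludes randomised participants without an outcome assessment, so the co-primary analysis is a complete-case analysis

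*Protocol article*

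**What the plan says.** All references are to the protocol article.

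- **Data management and statistical analysis plan**, principle: "Results will be analyzed as per intention-to-treat".
- Same section, next sentence. It applies to dropouts who lack an outcome assessment, and the reference group and the handling are given as: "those who completed the protocol but their data will be excluded from analysis".
- Same section, test: "Comparison between groups will be performed using Student’s" t test or the Mann–Whitney U test, depending on distribution. Neither test can use a participant whose outcome is missing.
- **Study outcomes**: the co-primary measures are "changes from baseline to end of study in mean 24 h systolic and diastolic blood pressure".
- **Study design**: "Study outcomes are assessed at the end of the eighth week".
- **Sample size calculation**: the 26 per group receives a 20% "inflation of this number to account for loss of follow-up and consent withdrawal", and the total is set at 60.

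**The concern.** The two adjacent sentences cannot both describe the primary analysis. Intention-to-treat keeps everyone randomised in the comparison. The second sentence removes people because of something that happened after randomisation.

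The article is not silent here in a way that an unseen analysis plan could fill. It fixes a rule, and that rule conflicts with the principle stated just before it.

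If those who leave differ in blood pressure response from those who stay, and loss differs between arms, the remaining groups are no longer comparable by randomisation. Only one arm breathes against a load, and the Intervention section lists possible discomforts of training, so unequal loss is conceivable. A result from participants with outcomes only could then carry a label that promises more protection than the analysis gives.

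**Working it through.** **1. The plan's own sample size.** The inputs come from the Sample size calculation section: "That study found an 8 mmHg difference in systolic blood pressure between the active treatment and the control group", SD 10 mmHg, power 80%, alpha 5% (taken as two-sided).
- Normal approximation: n = 2 × (1.960 + 0.842)² × (10/8)² = 24.5, so 25 per arm.
- Noncentral t: 25 per arm gives power 0.792 and 26 gives 0.807. The stated 26 reproduces.

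**2. How many outcomes may be missing.** The plan allows for between 60 − 2 × 26 = 8 and 20% of 60 = 12. With 30 per arm, a 20% loss leaves 24 per arm and power 0.774.

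**3. Who leaves the analysis.** The outcome is a change that ends at the week-8 recording, and the test needs an observed value. Anyone who drops out and has no outcome assessment is lost. Anyone who trains poorly or stops but is still measured at week 8 stays in the allocated arm. The set is therefore complete-case as allocated.

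**4. What the dropout comparison can show.** The difference detectable with 80% power, in SD units, is 2.80 × √(1/n₁ + 1/n₂).
- 8 against 52: 2.80 × 0.380 = 1.06 SD.
- 12 against 48: 2.80 × 0.323 = 0.90 SD.

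Only very large differences in observed characteristics would be detected, and the missing outcomes cannot be compared at all.

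**5. Possible size of the bias (assumptions, not figures from the article).** Take 30 per arm, systolic SD 10 mmHg and no true effect. The log-odds of dropout rise by b per SD of unfavourable change, and the intercept is set to give the stated loss. If q(z) is the dropout probability at standardised change z, the mean change among those retained is 10 × E[z(1 − q)] / E[1 − q]. Bias is the active value minus the sham value. Type I error comes from 100,000 simulated trials per row (two-sided t test at 5%).

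| Loss active / sham | b | Retained mean, active | Retained mean, sham | Bias favouring training | Type I error |
|---|---|---|---|---|---|
| 25% / 8% | 1 | −2.13 | −0.74 | 1.4 mmHg | 7.9% |
| 20% / 5% | 1 | −1.73 | −0.47 | 1.3 mmHg | 7.3% |
| 20% / 10% | 1 | −1.73 | −0.91 | 0.8 mmHg | 6.0% |
| 15% / 10% | 1 | −1.33 | −0.91 | 0.4 mmHg | 5.2% |
| 20% / 20% | 1 | −1.73 | −1.73 | 0 | 5.0% |
| 25% / 8% | 0.5 | −1.20 | −0.39 | 0.8 mmHg | 5.9% |
| 20% / 10% | 0.5 | −0.96 | −0.49 | 0.5 mmHg | 5.3% |

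To read b = 1 at 25% loss: 0.75 × (−2.13) + 0.25 × m = 0 gives m = 6.4, so dropouts' changes are about 8.5 mmHg worse than those of participants retained. That is strong selection. In the first row the errors fall almost wholly on one side: false claims for training reach 7.2%, against a nominal 2.5%.

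**The case against.** **The rule is narrow.** It removes only participants who both drop out and lack an outcome. A reader might infer a per-protocol set of people who finished training. The text does not support that, because poor adherers with a week-8 recording are kept as allocated. Nor does anything say that people who stop training are refused the recording. This stands and limits the point.

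**Differential dropout is not in the document.** The loss allowance is overall, and the discomforts are not split by arm. Both arms train for the same time under the same instructions, participants and assessors are blinded, and weekly visits and calls support retention. This also stands. With equal loss and equal selection there is no bias, and if outcomes are missing completely at random the complete-case contrast is unbiased.

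**Larger figures can be produced but are not supported.**
- Suppose 20% of the active arm is lost, those people do 8 to 10 mmHg worse, and the sham arm has no selection. The bias is then 0.20 × 8 = 1.6 to 0.20 × 10 = 2.0 mmHg, and type I error is about 8.9% to 11.1%.
- Suppose instead that 20% of the active arm is lost and gains nothing. An 8 mmHg effect in those measured then corresponds to 8 × 0.80 = 6.4 mmHg in all randomised.

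Both rest on one-sided assumptions that the article does not supply. Neither estimates the bias in this trial.

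**Imputation is not a complete cure.** Multiple imputation assumes missing at random, whereas the dropout modelled above depends on the unobserved outcome. The article describes no interim ABPM, so with arm and baseline alone such a method can recover little. This stands too and makes the sensitivity analysis essential.

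None of this reconciles the two sentences. Some missing outcomes are common in a trial analysed by intention-to-treat, but here the only stated handling is exclusion.

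**Conclusion.** The contradiction is certain and needs no assumption: the plan names intention-to-treat and prescribes a complete-case analysis for the co-primary outcomes. The consequence is conditional. Over the range of assumed dropout in the table, bias runs from 0 to about 1.4 mmHg in favour of training and type I error from 5% to about 8%, against a planned effect of 8 mmHg. Milder imbalance or weaker selection gives about 0.4 to 0.8 mmHg and 5% to 6%. These figures assume 30 per arm, a systolic SD of 10 mmHg, no true effect and dropout driven by the blood pressure change itself. They are not a bound, and no diastolic SD is given for a parallel calculation. A reader might infer that the trial's result will be biased or that its error rate is materially inflated; the article gives no arm-specific loss that would support this. The point should be fixed, but it does not invalidate the design.

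**What to change.** Replace the exclusion sentence with a rule that contains the following:

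1. Analyse all randomised participants as allocated, using the week-8 ABPM wherever it was obtained, including from those who stopped training.
2. Handle missing outcomes with a stated method valid under missing at random, such as multiple imputation or a likelihood-based model with arm and baseline ABPM.
3. Add a prespecified missing-not-at-random sensitivity analysis, for example imputing missing active-arm outcomes from the sham arm, or a delta adjustment over a stated range. The method in item 2 does not by itself remove bias from outcome-dependent dropout.
4. Keep the comparison of dropouts with completers as description, by arm. Report the complete-case result as supportive and do not call it intention-to-treat.

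The cost is wording, modest extra analysis and possibly a slightly wider interval or smaller estimate. No extra participants are needed. The Trial status section says that enrolment was still under way, and the randomisation section releases assignments only after data collection, so the rule could be settled before unblinding. The article also promises CONSORT reporting, which is a further reason to name the analysis set correctly.
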